# Physical activity as treatment for alcohol use disorders (FitForChange): study protocol for a randomized controlled trial

**DOI:** 10.1186/s13063-017-2435-0

**Published:** 2018-02-14

**Keywords:** Alcohol dependence, Randomized controlled trial (RCT), Exercise, Physical activity, Yoga

## Abstract

**Background:**

Help-seeking for alcohol use disorders (AUDs) is low and traditional treatments are often perceived as stigmatizing. Physical activity has positive effects on mental and physical health which could benefit this population. We propose to compare the effects of aerobic training, yoga, and usual care for AUDs in physically inactive Swedish adults.

**Methods:**

This is a three-group, parallel, single-blind, randomized controlled trial (RCT). In total, 210 adults (aged 18–75 years) diagnosed with an AUD will be invited to participate in a 12-week intervention. The primary study outcome is alcohol consumption measure by the Timeline Follow-back method and the Alcohol Use Disorders Identification Test (AUDIT). Secondary outcomes include: depression, anxiety, perceived stress, sleep quality, physical activity levels, fitness, self-efficacy, health-related quality of life, and cognition. Blood samples will be taken to objectively assess heavy drinking, and saliva to measure cortisol. Acute effects of exercise on the urge to drink alcohol, mood, and anxiety will also be assessed.

**Discussion:**

The treatment potential for exercise in AUDs is substantial as many individuals with the disorder are physically inactive and have comorbid health problems. The study is the first to assess the effects of physical activity as a stand-alone treatment for AUDs. Considerable attention will be given to optimizing exercise adherence. Both the feasibility and treatment effects of exercise interventions in AUDs will be discussed. The Ethical Review Board (EPN) at Karolinska Institutet has approved the study (DNR: 2017/1380-3).

**Trial registration:**

German Clinical Trials Register, ID: DRKS00012311. Registered on 26 September 2017.

**Electronic supplementary material:**

The online version of this article (doi:10.1186/s13063-017-2435-0) contains supplementary material, which is available to authorized users.

## Background

Alcohol use disorder (AUD) is a debilitating medical condition associated with negative health and social outcomes. Key features include an inability to control the amount of alcohol consumed, consumption that results in social or work-related problems, and tolerance or the need to drink increasing amounts of alcohol to obtain a desired effect [1]. Rates of help-seeking for AUDs are typically low and traditional treatments, such as medication and counseling, are often perceived as stigmatizing [2]. Treatment outcomes are also highly variable with many patients relapsing into the dependence syndrome following a period of abstinence [3]. Available evidence suggests that many people with an AUD are insufficiently active [4] and have impaired cardiorespiratory fitness [5]; factors contributing to a higher prevalence of cardiovascular disease, diabetes, and metabolic syndrome [6, 7]. Of particular concern, even individuals with milder forms of AUD experience an excess mortality rate twice as high than those without the disorder [8].

Physical exercise is known to benefit mental and physical health synergistically [9], and may be effective in the treatment of AUDs where multimorbidity – the presence of two or more health problems – is common. A growing body of evidence suggests that individuals with substance use disorders are interested in exercising and may derive benefits from regular exercise, both in terms of general health/fitness and dependence recovery [10]. Cross-sectional and prospective studies have consistently shown that physical activity is associated with better mental health [11, 12], and recent studies indicate that exercise may help reduce tobacco cravings and cigarette use [13].

The effects of exercise on alcohol consumption remain understudied and poorly understood. A recent meta-analysis identified 21 studies published between 1972 and 2016 examining physical activity interventions for AUDs [14]. The results indicated positive effects of exercise on depression and physical fitness, but no significant changes on measures of consumption; however, all analyses for this outcome were limited to three studies. Considerable study heterogeneity was observed, and no interventions had examined the effects of exercise alone with traditional treatments for AUDs [14]. In a recent narrative review, Giesen et al. concluded that exercise is both safe and feasible for patients with alcohol dependence, but called for larger controlled trials with comparisons of different types of exercise [10].

One issue that remains unclear is how different types of exercise influence treatment response. In mental health research, both aerobic exercise and strength training are effective in the treatment of mood disorders [15, 16], with effect sizes comparable to medication and psychological therapy [16]. However, these interventions may not be suitable for all patients with an AUD, especially those with little or no exercise experience. With its focus on flexibility, balance and posture, yoga is an increasingly popular form of exercise that could be particularly suitable for those with an AUD. Yoga meets the formal definition of “physical exercise” because it is purposeful, repetitive, and engaged in to improve fitness and/or health [17]. However, most forms of yoga include additional core elements, such as mindfulness, a focus on controlled breathing, and relaxation techniques. These features are known to have an influence on depressive symptoms and wellbeing [18]. Moreover, previous studies found significant heterogeneity in trials incorporating these mind-body approaches when compared with conventional aerobic or strength exercises [19]. For these reasons, it is important to compare the effects of yoga with conventional aerobic training.

This project builds on recently published data demonstrating the feasibility of yoga as an adjunct treatment for alcohol dependence [20]. Extending this work, we will conduct a randomized controlled trial (RCT) to examine the effects of two 12-week, supported physical activity interventions (yoga and aerobic training) on alcohol consumption in physically inactive adults with an AUD. A comparison group will receive standard treatment, described below.

### Key research questions

What are the effects of yoga and aerobic exercise on alcohol consumption in AUD patients?Does regular exercise reduce depression and anxiety, and improve self-efficacy in those with an AUD?Does exercise reduce stress and improve sleep quality in AUDs?Can exercise improve cognitive functioning in AUD patients?Does regular exercise improve health-related quality of life in AUD patients?What are the effects of exercise on cardiovascular risk factors and sedentary behavior?What are the effects of acute exercise on the urge to drink alcohol, mood, and anxiety? (nested study)What are participants’ subjective experiences of the intervention? (qualitative study)

## Methods

We adhered to the Standard Protocol Items: Recommendations for Interventional Trials (SPIRIT) guidelines in the preparation of this protocol (see Fig. 1 and Additional file 1 for the SPIRIT Figure and Checklist, respectively)

**Fig. 1 Fig1:**
[figure not shown]
Standard Protocol Items: Recommendations for Interventional Trials (SPIRIT) Figure. For the acute (nested) study, assessments will be administered on four occasions at baseline (indicated by XXXX): 1 h before, immediately before, 5 min after, and 1 h after the fitness test. See description within the manuscript for more details

### Setting and participants

Project coordination will take place at “Riddargatan 1: Center for Alcohol and Health”; an outpatient treatment clinic located in central Stockholm specializing in AUDs. The clinic opened in 2011 and is staffed by physicians, psychologists, and allied health workers with expertise in the treatment and management of addictive behaviors, including AUDs. All participants will have a diagnosed AUD, based on *Diagnostic and Statistical Manual of Mental Disorders, version 5* (DSM-5) criteria. In addition to this criteria, participants must also meet the threshold for hazardous drinking, which is defined by the Swedish National Institute for Public Health as either (a) consumption of 9 or 14 standard drinks per week for women and men, respectively, or (b) binge drinking at least once during the past month (that is >4/5 standard drinks for men and women, consumed on a single occasion). Recruitment will occur through advertisements placed in waiting rooms in primary and occupational healthcare centers in Stockholm, and media outlets, e.g., local newspapers. Participants will not be recruited directly from the specialist outpatient clinic (Riddargatan 1) because these are individuals already seeking and expecting to receive specialized treatment. Recruitment will commence in January 2018 and continue throughout the year. The study will conclude in December 2019.

### Study design, randomization, and blinding

This is a three-group, parallel, single-blind, RCT to compare the effects of three 12-week interventions (yoga, aerobic training, and treatment as usual (TAU)) on alcohol consumption. The proposed flow of participants through the trial is shown in Fig. 2. Assessments will be made at baseline (pre randomization) and post treatment (week 13). The randomization sequence will be computer generated and performed externally by a statistician at the Karolinska Institutet. A researcher not involved in the trial, but located at the clinic where the study will be managed, will then receive the allocation in sequentially numbered, opaque envelopes. In this way, the allocation sequence will be concealed from the person responsible for randomizing study participants. Trained research assistants, including a qualified nurse or psychologist, will administer each assessment in person at Riddargatan 1. The 12-week “treatment” will commence approximately 1 week after the baseline assessment when participants begin training/treatment (baseline physical activity levels will be measured for 1 week before this, see description below). To optimize recruitment and minimize dropouts, those randomized to TAU will be offered the 12-week exercise intervention after they have completed the follow-up assessment. The study endpoint is week 13 (post-treatment). All participants will be aged 18 to 75 years and residents of Stockholm County. Treatment allocation will not be concealed from either participants or the researchers conducting the baseline assessments. However, as a different research assistant will perform the post-treatment assessments, follow-up assessors will be blind to group allocation. Unblinding will only occur in the event that a participant chooses to withdraw from the study.

**Fig. 2 Fig2:**
[figure not shown]
Participant flow diagram

### Procedure

Prior to starting the RCT, a pilot study (*n* = 15) will be conducted involving an intervention identical to that used in the main study. The purpose will be to test the study protocol and obtain feedback from participants on the feasibility of the interventions. Interested participants will be advised to contact the project coordinator (a qualified nurse and clinician) for information about the trial. An initial telephone-based screening interview will be performed by the coordinator to determine eligibility based on age, health status, exercise participation history, and alcohol use. Those eligible will be invited to attend the clinic, where the purpose of the study will be explained in detail – verbally and in writing – and a baseline assessment completed after obtaining informed consent.

#### Exclusion criteria

Patients with known cardiovascular risks (e.g., a history of heart disease), hypertension (e.g., systolic blood pressure > 200 mmHg and/or diastole blood pressure > 110 mmHg), those with musculoskeletal injuries preventing exercise, those undertaking current regular exercise participation (defined here as two or more planned exercise sessions per week during the past month), and those requiring or receiving specialist psychiatric care (e.g., for psychosis) or with a primary somatic complaint will be excluded. A general health questionnaire developed by the Swedish Institute of Sport and Health Sciences (GIH) will be used to assess cardiovascular and related health risks. Patients who are at suicide risk, assessed initially by a single question “have you recently had thoughts about harming yourself?” will also be excluded and referred to a clinician for support. After completing the baseline assessment (approximately 90 min – see below), eligible participants will be requested to provide a blood sample at a registered laboratory, and return two saliva samples (morning and evening) using a sampling kit provided to them. On the same day all participants will also complete a baseline fitness test, and will be fitted with accelerometers to objectively measure physical activity levels for 1 week before starting the intervention.

#### Baseline and follow-up assessments

Alcohol consumption assessed by the Timeline Follow-back method (TLFB) [21] is the primary study outcome. Using a calendar, respondents provide retrospective estimates of their daily drinking over the previous month. The TLFB has been evaluated with clinical and non-clinical populations [22]The Alcohol Use Disorders Identification Test (AUDIT): a 10-item screening instrument to assess alcohol consumption, drinking behaviors, and harms caused by alcohol use [23]Demographics: age, gender, occupation, marital status (baseline only)General health survey (developed by the GIH) for the assessment of cardiovascular disease and musculoskeletal problems (baseline only). Examples of questions include: have you ever been treated for heart disease? Do you have any injuries that prevent or interfere with exercise?The International Physical Activity Questionnaire (IPAQ) [24]: seven questions assessing the frequency and amount of time spent doing light, moderate, vigorous physical activity, and time spent sitting during the past 7 daysThe Hospital Anxiety Depression Scale (HAD) [25]: 14 items scored 0–3 based on how the respondent felt during the past week. Examples: I feel tense or “wound up”; I get a sudden feelings of panic; I feel as if I am slowed downThe Perceived Stress Scale (PSS) [26]: 10 items scored 0–4 based on how the respondent felt during the past month. Examples: how often have you felt nervous and “stressed”?; how often have you felt that you were on top of things?; how often have you been able to control irritations in your life?The Insomnia Severity Index (ISI) [27]: seven items scored 0–4 based on the respondent’s self-rated sleep quality during the past 2 weeks. Examples: difficulties falling asleep; difficulties staying asleep; problems waking up too earlyThe SF-12 Health Survey [28]: 12 items assess functional health and wellbeing from the respondent’s perspective. The SF-12 covers eight domains: vitality, physical functioning, bodily pain, general health perceptions, physical role functioning, emotional role functioning, social role functioning, and mental healthThe Alcohol Abstinence Self-Efficacy Scale [29]: 12 items scored on a 5-point Likert scale assess how “tempted” or “confident” the respondent feels that they would be to drink in certain situationsThe Cogstate Brief Battery (CBB): a standardized test of cognitive functioning that measures four key domains: psychomotor function, attention, visual learning, and working memory [30, 31]. Participants complete the 12-min test on a laptop computer under supervision

#### Objective assessment of physical activity

In addition to the IPAQ self-report questionnaire, physical activity, and sedentary behavior will be objectively recorded using an accelerometer (ActiGraph GXT3). All participants, including TAU participants, will be instructed to wear the device for seven consecutive days 1 week before the first exercise class (baseline assessment of activity), 1 week after (week 13). Accelerometry is a non-invasive method of monitoring human rest/activity cycles, and the device will estimate gross motor activity during the intervention. This data will enable more sophisticated analyses of the associations between exercise, physical activity, sedentary behavior, and alcohol consumption to be explored. To obtain an objective intensity measure of the prescribed physical activity sessions, data on heart rate will be collected by providing Polar heart-rate monitors to participants randomized to yoga or aerobic training. Because it is not feasible to gather heart-rate data from all participants for the entire duration of the trial, the monitors will be worn for 1 week during the middle of the participant’s 12-week treatment, thereby providing an “average” indicator of activity intensity. These data will be collected by a research assistant who will meet the participants after 6 weeks.

#### Biomarkers

From blood samples, standard biomarkers of heavy drinking will be taken at each assessment: phosphatidyl ethanol (PEth), γ-glutamyl transferase (GGT). Changes in blood cortisol level (stress) will be assessed at each time point, plus blood lipid profiles and blood glucose as markers of health status.

#### Fitness and general health assessment

Fitness will be assessed pre and post intervention using a graded, sub-maximal exercise test to predict VO_2_max using the method described by Ekblom-Bak et al. [32]. In addition, body weight, height, waist and hip circumference, and blood pressure will be recorded. Participants will be instructed to avoid alcohol consumption for 24 h before the test. The rationale for assessing fitness is to determine whether the intervention leads to a measurable change in aerobic conditioning, and to explore possible associations between fitness and different study outcomes. The testing procedure will take place at Riddargatan 1, supervised by a qualified exercise physiologist.

### Acute exercise study

Alcohol “urges” – that is, a strong craving for alcohol – have been shown to predict relapse in dependent patients, and recent studies suggest that short bouts of exercise can reduce urges for tobacco in smokers [33, 34]. To examine the short-term effects of acute exercise on alcohol craving, mood, and anxiety in those with an AUD, participants will complete the eight-item Desire for Alcohol Questionnaire (Shortened) [35], the 30-item Profile of Mood States – Brief Form (POMS-B) [36], and the state subscale of the State-Trait Anxiety Inventory (STAI-Y1) [37] on four occasions: 1 h before the fitness test, immediately before, 5 min after, and 1 h after the test. During the final minute, Borg’s Rating of Perceived Exertion will be administered; a single-item Visual Analogue Scale, where respondents indicate how hard they feel they are currently exercising. The fitness test will take about 15 min to complete. For feasibility reasons, this will be a single-arm, acute exercise study, where within-group changes over time are examined.

#### Exercise intervention

All physical activity classes include between 5 and 40 people. Participants will be requested to attend three exercise sessions per week for 12 weeks. To maximize adherence and reduce dropout, participants within each exercise group will be given a choice of either three yoga-based classes, or three aerobic classes of comparable intensity and duration. One advantage of this approach, is that participants will have a greater selection of times and locations for their training. Removing this choice could make the intervention impractical for some participants and reduce adherence. All sessions will be undertaken at SATS; a modern fitness center with multiple locations throughout Sweden. To ensure that classes are delivered in a consistent and safe manner, all trainers complete a course in personal training administered by “SAFE” (www.safe-education.se). The exercise options include: beginner to intermediate-level yoga sessions that coordinate breathing and movement in a dynamic flow between different yoga positions, and “Body balance” classes which combine conventional yoga with stretching and pilates movements. For aerobic training: “spinning” classes will be offered, consisting of aerobic exercise on stationary cycles performed in groups, “Energy” classes – choreographed aerobic training to music consisting of dynamic, whole-body movements designed to increase heart rate, and “Body-combat” classes, consisting of aerobic training based around martial arts movements (kicks, punches) and related training (sit-ups, push-ups, body-weight squats, etc.).

#### Adherence

Data on participation in all exercise sessions will be collected via the SATS electronic entry system which records the type of session attended. At 12 weeks, participants receiving the exercise intervention will be encouraged to continue the regimen but without follow-up or monitoring. In addition, participants will be offered three 45-min sessions (at weeks 1, 4, and 8, approximately) with a SATS personal trainer to monitor progress and help maintain motivation.

#### Treatment as usual (TAU)

Participants randomized to TAU will be asked to contact by phone an alcohol information service “Alcohol Help” (www.alkoholhjalpen.se). A qualified alcohol treatment specialist – nurse, psychologist or similar – will advise participants about the availability of different treatment options for their alcohol-related problem. These options include referral to a general medical practitioner, brief telephone counseling, referral to Alcoholics Anonymous or an Internet self-help website, or to a specialist alcohol treatment clinic. Participants may choose to pursue any (or none) or these treatment options. The treatment specialist will be given the participant’s AUDIT scores to facilitate feedback, and will contact each TAU participant on three occasions (once a month) to follow up their treatment progress. The researchers will have no influence over the treatment choices made by those randomized to TAU.

#### Follow-up assessments and qualitative study

All participants will be contacted by a research assistant at week 6, about half way through the intervention, and invited to attend a short meeting. The purpose will be to (1) hand out the heart-rate monitors with instructions for use and (2) to assess changes in alcohol consumption. Participants who indicate a 50% or more increase in the total volume of alcohol consumed during the past month assessed by the TLFB will be removed from the trial and offered additional clinical support. This assessment will be made by a research assistant with qualifications in nursing or psychology. Participants will be contacted again during week 13 and invited to attend a final follow-up interview. Those who decline will be invited to complete a phone interview or given a shortened baseline questionnaire to return via mail (TLFB, HAD, and physical activity only). Participants will be contacted using a combination of phone calls, emails, and text messaging up to six times over a 2-week period. In addition to collecting quantitative data, we propose to complement these data with a qualitative study. At the post-treatment assessment we propose to conduct semi-structured interviews with participants to determine which aspects of the study, including the exercise intervention, assisted them (or not) and why. During this process, we also propose to assess the acceptability of the interventions among men and women, and younger and older participants. Initial selection will be based on the order of inclusion into the trial. Since we aim for an even distribution across treatment groups, age, and gender, this will also be considered in the selection process. This is a purposive sample; interviews will be analyzed continuously during the data collection period, and the exact number of participants will be determined when “saturation” is reached and no new themes emerge from the interviews. The qualitative part of the study, i.e., developing the interview guide, selecting the participants, data collection, and analyzing the interviews, will be supervised by an experienced qualitative researcher.

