### Statistical analyses and power calculation

Baseline participant characteristics stratified by treatment group will be presented. Group differences will be tested using *t* tests for continuous variables and chi-square tests for categorical outcomes. Parametric test assumptions will be examined and reported. Non-parametric data will be transformed or alternatively analyzed using non-parametric statistical tests. Multiple imputation will be used to replace missing internal values where appropriate. Within-group changes in the primary outcome (alcohol consumption) and secondary outcomes (depression, anxiety, cognitive ability, etc.) will be analyzed using paired-sample *t* tests. To address the primary research question, intention-to-treat analyses will be performed. The effect of group allocation on alcohol consumption and all secondary outcomes at 3-month follow-up will be assessed using mixed linear regression models (logistic for binary outcomes), using both the mean difference (baseline to 3 months) and total scores as dependent variables. Where the total score is used as the outcome, baseline group differences in covariates will be adjusted. As adherence may be sub-optimal, per-protocol analyses will also be presented. Data from individual accelerometers will be pooled to objectively assess changes in physical activity levels before and after treatment. We propose to conduct sub-group analyses based on participant gender and age to assess the effects of these variables on alcohol consumption. All analyses will be performed using SPSS 22.0. All tests will be two-sided and *P* values of less than 0.05 considered statistically significant.

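### Removing participants whose drinking has risen by week 6 is a post-randomisation exclusion on the primary measure and conflicts with the intention-to-treat analysis

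*Protocol article*

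**What the plan says.** The section on follow-up assessments and the qualitative study sets a week-6 meeting for all participants, in all three arms. Those with "50% or more increase in the total volume of alcohol consumed during the past month assessed by the TLFB will be removed from the trial"; in full, they "will be removed from the trial and offered additional clinical support".

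Three other statements bear on this:

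- **Outcome** (Baseline and follow-up assessments): "Alcohol consumption assessed by the Timeline Follow-back method (TLFB) [21] is the primary study outcome".
- **Timing** (Study design, randomization, and blinding): baseline precedes randomisation, and the endpoint is week 13.
- **Analysis** (Statistical analyses and power calculation): "To address the primary research question, intention-to-treat analyses will be performed". Mixed models are fitted "using both the mean difference (baseline to 3 months) and total scores as dependent variables". Paired t tests are planned for change within each arm. On missing data: "Multiple imputation will be used to replace missing internal values where appropriate".

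**The concern.** The rule acts after randomisation, and its trigger is an interim reading of the primary measure. If removed participants have no week-13 value, the analysed set is selected on how well each person was doing on treatment, and that selection can differ by arm.

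- **If exercise works**, usual care loses more of its worst drinkers than the exercise arms do, and the contrast tends toward the null.
- **If an exercise arm increases drinking**, that arm loses more, and part of the harm is hidden. That matters for a stand-alone treatment of alcohol use disorder.
- **If nothing works**, the arms lose equal shares and the between-arm contrast stays unbiased. The within-arm paired tests, run on those left, would still lean toward a fall in drinking, because people whose volume rose have been taken out.

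**Working it through.** **1. The texts side by side.** Intention to treat means that everyone is analysed as randomised. The follow-up section takes a group out of the trial at week 6, not merely off the allocated programme. The only post-treatment assessment is week 13. No sentence says that removed participants are recontacted, retained or imputed. The plain reading, though not stated outright, is that they have no endpoint value.

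**2. Inputs for the size.** The article gives no SD or correlation for drinking volume, so this part is illustrative.

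- From the article: a 50% threshold (ln 1.5 = 0.405 on the log scale) and a planning effect of 0.3 SD.
- Assumed: log volume at baseline, week 6 and week 13 is jointly normal. SD s is 0.6 or 0.8. Each correlation is 0.5, 0.6 or 0.7, with baseline/week 13 no larger than the other two. Usual-care drift is 0, −0.3 or −0.5 log units. The effect is the same at weeks 6 and 13. The rise is measured against baseline, removed people have no week-13 value, and there is no other dropout.

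**3. Formulas.** Let D be week-6 minus baseline log volume, with mean m in an arm and SD σ = s√(2(1 − r₀₆)).

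- Share removed = 1 − Φ(z), where z = (0.405 − m)/σ.
- Mean change to week 13 among those kept = true mean change − b·σ·λ(z), where λ(z) = φ(z)/Φ(z) and b = (1 + r₆,₁₃ − r₀₆ − r₀,₁₃)/(2(1 − r₀₆)).
- For the unadjusted total score, replace b by b′ = (r₆,₁₃ − r₀,₁₃)/(2(1 − r₀₆)).

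**4. Worked case: benefit of 0.3 SD.** Take s = 0.8, r₀₆ = 0.6, r₀,₁₃ = 0.5, r₆,₁₃ = 0.7, drift 0. The true difference is 0.3 × 0.8 = 0.24, and σ = 0.8 × √0.8 = 0.716.

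- Usual care: z = 0.405/0.716 = 0.567, removed 29%, λ = 0.476.
- Exercise: z = (0.405 + 0.24)/0.716 = 0.902, removed 18%, λ = 0.325.
- Change score: b = 0.6/0.8 = 0.75. Loss = 0.75 × 0.716 × (0.476 − 0.325) = 0.081. Retained = (0.24 − 0.081)/0.24 = 66%.
- Total score: b′ = 0.2/0.8 = 0.25. Loss = 0.027. Retained = 89%.

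**5. Worked case: no change in any arm.** Take s = 0.8, r₀₆ = r₀,₁₃ = 0.5, r₆,₁₃ = 0.7. Then σ = 0.8, z = 0.507, 31% are removed, λ = 0.506 and b = 0.7. Mean change among those kept = −0.7 × 0.8 × 0.506 = −0.28 log units, an apparent fall of about 25%. At the mild end (s = 0.6, r₀₆ = 0.7, b = 0.5): σ = 0.465, z = 0.872, 19% removed, λ = 0.337, change −0.08, a fall of 7 to 8%.

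**6. Whole grid** (simulation, 1,000,000 per arm per scenario):

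| | Benefit 0.3 SD | Harm 0.3 SD |
|---|---|---|
| Removed, usual care | 3–31% | 3–31% |
| Removed, exercise | 1–21% | 6–42% |
| Share of true effect seen: change score | 66–96% | 56–92% |
| Unadjusted total score | 86–101% | 82–101% |
| Baseline-adjusted total score | 75–98% | 67–96% |

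Over the same grid the formulas give 65–95% (change score) and 86–100% (unadjusted total) under benefit. The one-point differences are simulation error. With no effect and no drift, 19–31% of each arm is removed, the between-arm difference is within 0.002 log units of zero, and the spurious within-arm fall is 7–25% (0.13–0.35 SD).

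**7. Imputation.** Under benefit, imputing week 13 by arm from baseline and week-6 TLFB restores 99–101% of the effect. Imputing from baseline alone gives 74–98%.

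**The case against.** **The conflict is inferred.** Shortly after the removal rule, the same section says participants will be contacted in week 13, with phone and mail routes that include the TLFB, and it exempts no one. Removal might be meant to end the programme only. This is possible, but the wording is removal from the trial, and staff following it would have no reason to seek a week-13 value.

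**The analysis could absorb it.** Removal depends only on baseline and week-6 TLFB, both observed, so a likelihood model or an imputation using week 6 would recover the effect, and such detail is commonly left to the analysis plan. That is right as far as it goes. But the models are described with the change or the 3-month total as outcome, and nothing commits to using week 6. Nor can an analysis plan restore data that a conduct rule stops staff collecting. The fault is the stated rule, not the missing imputation detail.

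**The sizes lean high.** This stands in part. If only half the effect is present at week 6, the share seen is 82–98% (change score), 93–102% (unadjusted total) and 86–100% (baseline-adjusted). Adding an illustrative baseline cut at −0.5 SD, for entry on hazardous drinking, puts usual-care removal at 1–21% (median about 8%) and median retention at 94–97%. With drift −0.5, removal in usual care is 3–13%. The largest within-arm artefact needs zero drift and complete-case analysis, and those tests are not the primary comparison.

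**The bias is conservative under benefit and absent under the null.** True between arms. It offers no comfort if an exercise arm does harm, where the same mechanism hides part of it.

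**The rule protects patients.** Referral is right, but it does not require ending outcome follow-up.

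**Conclusion.** The concern holds. The article states a post-randomisation removal triggered by the primary measure and gives nothing that reconciles it with the promised intention-to-treat analysis. That conclusion rests on the text and needs no numerical assumption beyond the plain reading of removal.

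The size does rest on assumptions. The change score, one of the two named dependent variables, is attenuated in every benefit and harm scenario examined, from slightly to by about a third under benefit and by up to about 44% under harm. The unadjusted total score suffers less, and not at all when week 13 correlates equally with baseline and week 6 (b′ = 0). The between-arm comparison under the null is unaffected.

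This should be corrected before recruitment: it touches the primary outcome, and week-13 values not collected cannot be recovered later.

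**What to change.** Keep the week-6 trigger and the offer of support, but separate them from trial participation. Suggested wording: *Participants who meet this criterion are offered clinical support and may stop the allocated intervention. They remain in the trial, are invited to the week-13 assessment by visit, phone or mail, and are analysed in their randomised group.* Report the number meeting the trigger in each arm. For any who still lack week-13 data, include week-6 TLFB in the imputation model.

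The cost is a few sentences, since the week-13 contact routes already exist. The one downside is that some week-13 values will reflect the extra clinical support. The count by arm lets readers judge how much.
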